### Sample size determination

The sample size is determined considering both the intervention and control using a formula recommended for dichotomous outcome variable. We assumed that implementation of community based intervention program to prevent domestic VAW is superior as compared with the standard service [51]. In addition, we considered 5% margin of error, 95% significance level and 80% power.$$ N=2\times {\left(\frac{z_{1-\alpha }+{z}_{1-\beta }}{\mathrm{d}\hbox{-} {\delta}_0}\right)}^2\times p\times \left(1-p\right) $$

Where as; N is the sample size of each group, P is prevalence in standard intervention (control arm), d: the real difference between two treatment effects (d = P_o_-P_x_); 22%–9% = 13% = 0.13: study done in Uganda (22%) in the standard intervention group [52]; δ_0:_ statistical acceptable margin (5%); ɑ: significance level at 95% (ɑ = 1–0.95 = 0.05 = 1.645), ß_:_ 80% power (ß = 1–0.8 = 0.2 = 0.845. Then, 15% is added for potential non-achievements. Furthermore, due to the multistage sampling, design effect is considered to boost the power and precision that taken from the design effect of women experienced physical or sexual violence in the study area (Amhara region) in the last 12 months was 1.11 [53]. Eventually, a total 1269 women is obtained for the three arms (i.e. 423 for each group). The number of qualitative study participants will be determined by information saturation. However, a minimum 12 in-depth interviews and two focus group discussions (FGDs) (male versus female groups) which comprise 8–10 discussants will be conducted.

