### Sampling procedure

Multistage, stratified and systematic sampling will be used to recruit study participants at their permanent place of residence. Three districts are selected out of nine districts in Awi zone (comprehensive intervention, active comparison and control). Then, six sub-districts (two sub-districts from each district) will be selected purposefully considering appropriateness for intervention, resource, and geographical non-proximity to control information contamination between intervention and controls. Then, sub-districts will be stratified (urban versus rural) to control the awareness level, access to information and community traditional gender norm variability between urban and rural dwellers. After that, the sample of the group will be proportionally allocated to size of each selected sub-district. The number of eligible households for this study will be identified using the community based health extension workers registry. Eventually, systematic sampling will be employed to select actual study participants at household level. Unique code will be given to selected households for intervention monitoring and finally endline evaluation purpose. In the meantime, if two married women are present in one household, only one woman will be selected using lottery method for interview.

Purposive sampling method will be used to select study participants for in-depth interview, key informant interview (KII) and FGDs. Community leaders will be consulted and actively involved on the recruitment of the most knowledgeable community representatives for in-depth interview, KII and FGDs. It will be conducted to explore individual and community perception about domestic VAW, sex negotiation, decision making, community gender norm, wife beating attitudes and community responses.

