
### Data processing and statistical analysis

Both baseline and endline data will be checked and edited for completeness and consistency at field as well as at office. Explanatory and outcome variables will be clearly predefined prior to data entry, in which domestic VAW will be coded as if a woman reports at least one type of experience of either physical, psychological or sexual violence coded as “Yes = 1” and “No = 0”. Similar coding will be done for physical, sexual and psychological domestic violence against women to carry out subgroup analysis. On the other hand, women’s wife beating accepting attitude will be measured using six questions or measurements, and also if women respond at least one justifying wife beating [58, 59, 61]. Similarly women autonomy will be measured in four indicators such as economic decision-making, reproductive health service utilization decision-making, extent of freedom of movement, and women’s attitudes toward violence [54].

Then, data will be entered in Epidata (3.5.1) and exported to SPSS (23.0) for further cleaning and analysis. Multiple imputation will be done to handle missing data as necessary. Descriptive statistics, binary and multiple logistic regressions and Intention to Treat Analysis (ITTA) will be computed. Moreover, Difference in Differences (DID) will be calculated to determine the net intervention effect. Finally, statistical significance of intervention effect will be measured using adjusted prevalence ratio, adjusted odds ratio/risk ratio at 95% confidence interval (CI) and *P*-Value less than 0.05. On the other hand, qualitative data will be transcribed through playing and replaying the voice recorder and also narrating the note taken during interviews or FGDs. The voice recorder audio will be listen as much as possible in quiet place. It will be transcribed independently by research assistant and principal investigator according to the verbatim of participants'. Then transcribed qualitative data will be translated from local language (Amharic) to English. The quotes will be narrated and cited using participant’s code. Thematic areas will be identified and arranged based on their themes. Ideas will be color coded, and then merged accordingly. Qualitative data will be analyzed or arranged using Nvivo software.

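### The intervention effect is judged by woman-level ratios at P < 0.05 with no named allowance for clustering, although each arm is two sub-districts of a single district

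*Protocol article*

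**What the plan says.** **Allocation (Sampling procedure).** Arms are whole districts: "Three districts are selected out of nine districts in Awi zone (comprehensive intervention, active comparison and control"). Within them, "six sub-districts (two sub-districts from each district) will be selected purposefully", and "the sample of the group will be proportionally allocated to size of each selected sub-district".

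**Sample size (Sample size determination).** Correlation within areas is accepted here: "due to the multistage sampling, design effect is considered to boost the power and precision". The factor comes from an outside source for the region, where the design effect "in the last 12 months was 1.11". The result is that "a total 1269 women is obtained for the three arms (i.e. 423 for each group").

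**Analysis (Data processing and statistical analysis).** The outcome is coded yes or no for each woman. The methods are listed as "Descriptive statistics, binary and multiple logistic regressions and Intention to Treat Analysis (ITTA) will be computed". DID is then named for the net intervention effect. The decision rule is that "statistical significance of intervention effect will be measured using adjusted prevalence ratio, adjusted odds ratio/risk ratio at 95% confidence interval (CI") and P below 0.05. No mixed model, GEE, cluster-robust error or cluster-level comparison is named.

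**Follow-up (phase and monitoring table).** The same women are to be interviewed again at endline.

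**The concern.** The intervention acts on communities: public mobilization, trained local leaders, and health extension workers who serve a sub-district. Anything that shifts reporting or violence across one sub-district moves all its sampled women together. A standard error that treats about 423 women per arm as independent counts that one shift as hundreds of separate observations.

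The protocol allows for this correlation when it counts women and then does not carry it into the rule by which it declares an effect. The study could report a significant effect of the package, or of husband involvement (Arm 1 against Arm 2), that is only variation between sub-districts. The protocol plans to scale up what succeeds.

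**Working it through.** **1. The plan's own figure.** With p = 0.22, d = 0.13, margin 0.05, z = 1.645 and 0.842:

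N = 2 × ((1.645 + 0.842)/(0.13 − 0.05))² × 0.22 × 0.78 ≈ 331.5; × 1.15 = 381.3; × 1.11 = 423.2.

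This reproduces 423 per arm, so clustering enters the sizing once, as 1.11.

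**2. Cluster size.** 423/1.15 = 367.8 evaluable women per arm, and 367.8/2 = 183.9, about 184 per sub-district. This assumes the whole 15% allowance is lost and the two sub-districts are of equal size; the protocol gives no actual split.

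**3. Endline comparison with independent-woman errors.** Design effect DEFF = 1 + (184 − 1) × ICC. True two-sided error of a nominal 5% test = 2(1 − Φ(1.96/√DEFF)). The ICCs are assumptions.

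| ICC | DEFF | True error | Correct CI width ÷ naive width (√DEFF) |
|---|---|---|---|
| 0.005 | 1.92 | 16% | 1.38 |
| 0.01 | 2.83 | 24% | 1.68 |
| 0.02 | 4.66 | 36% | 2.16 |

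With no dropout (211.5 per sub-district) the formula gives 17%, 27% and 39%. Simulation at that size (40,000 runs per setting) gave 17%, 26–27% and 39%.

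**4. The protocol's 1.11 as the trial's design effect.** 2(1 − Φ(1.96/√1.11)) = 6.3%. This needs an ICC of 0.11/183 = 0.0006. If 1.11 came from a survey with 10 to 30 women per cluster (an assumption; the cluster size is not given), the ICC is 0.11/9 = 0.012 to 0.11/29 = 0.004. DEFF here is then 3.24 to 1.69, and the error 28% to 13%.

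**5. DID on pooled records.** Let CAC be the correlation of a sub-district's effect between baseline and endline, and ρ the within-woman correlation. The ratio of true to naive variance is

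q = 184 × ICC × (1 − CAC) + (1 − ICC)(1 − ρ), with true error 2(1 − Φ(1.96/√q)).

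| CAC | ρ | ICC 0.005 | ICC 0.01 | ICC 0.02 |
|---|---|---|---|---|
| 0.5 | 0 | 10% | 16% | 24% |
| 0.8 | 0 | 7% | 9% | 13% |
| 0.5 | 0.5 | 4.5% | 9.9% | 20% |
| 0.8 | 0.5 | 1.8% | 3.5% | 7.7% |

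The range is about 2% to 24%. Three of the twelve entries are below 5%.

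**6. DID that models pairing but not clusters.** Divide q by (1 − ICC)(1 − ρ). At ICC 0.02 and ρ = 0.5:
- CAC 0.8: (0.736 + 0.49)/0.49 = 2.50, error 22%.
- CAC 0.5: (1.84 + 0.49)/0.49 = 4.76, error 37%.

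**7. Degrees of freedom.** Six sub-district changes less three arm means leave 3 df (critical value 3.18). A two-arm comparison has 4 − 2 = 2 df, and a three-arm analysis with an urban/rural term has 6 − 3 − 1 = 2 df (critical value 4.30). The woman-level rule uses 1.96.

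**The case against.** The protocol never says that the logistic regression is ordinary, and it names DID, not logistic regression alone, for the net effect. It also lists prevalence and risk ratios, which a standard logistic fit does not give directly, so the model is not fully fixed. The handling of standard errors is often left to an analysis plan or full protocol, and neither is shown.

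A reader might therefore infer more than the text supports: that the plan commits to ordinary logistic regression as the only effect analysis, that every interval will be too narrow, and that false positives will be well above 5%. The documents do not support that. DID removes stable differences between sub-districts. If the pairing of women is ignored, a strong within-woman correlation can bring the error below 5%. The one clustering figure printed, taken at face value, gives about 6%.

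These points limit the size of the problem but do not remove it. The section does more than stay silent: it fixes the outcome coding, the regressions, the effect measures and the significance threshold, and the decision rule attaches to the adjusted ratios. Followed as written, with woman-level errors, the endline ratio has too narrow an interval at any positive ICC. A conservative pooled DID is two omissions offsetting each other by chance. An unseen analysis plan could add a cluster method but could not undo one district per arm.

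**Conclusion.** The point holds in a limited form. The stated decision rule uses woman-level ratios with no named allowance for clustering, in a design with two sub-districts per arm that the protocol itself treats as clustered when sizing.

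For an endline ratio the direction is certain for any positive ICC; the size is not, because no ICC is given. The 16% to 36% range rests on assumed ICCs of 0.005 to 0.02 and 184 women per sub-district. For DID even the direction depends on how much of the cluster variance changes over the year, and on whether pairing is modelled.

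Separately, arm and district coincide completely. This also applies to the husband-involvement contrast, which compares one district with another.

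**What to change.** In Data processing and statistical analysis:

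1. Base inference on the intervention effect on the six sub-district baseline-to-endline changes, using t with 3 df (3.18), or 2 df (4.30) for a two-arm comparison or if an urban/rural term is included. An equivalent mixed model with a sub-district-by-period random effect and small-sample degrees of freedom would also serve.
2. Report woman-level adjusted ratios as descriptive, without a P < 0.05 claim.
3. State as a limitation that with one district per arm no analysis can separate district from intervention, including for husband involvement. Taking the control sub-districts from two districts would not cure this, because both active arms would still have one district each.

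**Cost.** No extra women or fieldwork, but much wider intervals and much lower power. To illustrate, take an endline test of 22% against 9% with 423 women per arm and no margin. The woman-level half-width is 0.048 and the nominal power is over 99%. A sub-district t test on 2 df has a half-width of 0.111 and power of about 72% at ICC 0.0005, and 0.186 and about 39% at ICC 0.01. Simulation put the endline 2-df test's error at 4.8% to 5.5% for ICCs from 0 to 0.05, but only with no variance between districts. Likewise, the analysis of changes is valid only if change does not vary between districts, which this design cannot test. The protocol should state both the power loss and this assumption.

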### Implementation Design of the Community Based Intervention

Evidence from clustered randomized controlled trials, community based quasi-experimental trials, longitudinal studies and systematic review on domestic VAW have been used to design intervention. In addition, recommendation of various community based research evidence, WHO recommendations, existing legal sanctions or policy documents (constitution, civil code, family laws and standard operation procedure to respond and prevent domestic VAW) will be used to implement the intervention. Intervention will be implemented using culturally appropriate and integrating with existing innovative community based health extension program. Interventions will be more focused on traditional gender norm, negotiation skills and involve men on domestic violence prevention activities. The intervention implementation will have contextualization, tool development and validation, advocacy, stakeholders’ engagement and overall community mobilization activities.

### Advocacy meeting and stakeholders engagement

Advocacy meeting will be held to enhance awareness about domestic VAW problem, socioeconomic consequences, political implications, evidence based prevention strategies and country legal sanctions towards VAW. The advocacy meeting will be held every three months regularly for a year. It will create an entry point into the community and also involve stakeholders. Both the zonal and district health offices, women and child affair offices, police and security, office of justice, agriculture and land management office, women lawyer associations, nongovernmental organizations, community representatives (religious fathers, local leaders and elders) will be considered as potential stakeholders. However, stakeholder analysis will be made in Awi zone perspective to identify key stakeholders. Then, identified key stakeholders will be expected to be actively involved on the implementation process as per their hierarchy. Gender expert from health office and women and children affair office will be actively involved in the intervention implementation process.

The intervention will be implemented to address the risk factors according to Ecological Model (individual, relationship, community and societal level factors). Furthermore, piloting implementation intervention will focus on the five domain of implementation research domains (intervention, inner, outer, individual behavior and process settings) which clearly illustrated on Consolidated Framework for Implementation Research (CFIR) model, and presented in detail as additional file (see Fig. 4).

**Fig. 4 Fig4:**
[figure not shown]
Schematic presentation of Interacting domains using CFIR

Arm 1: Comprehensive intervention group: comprehensive intervention to prevent domestic VAW and enhance existing policies will be conducted. The intervention will be focused on physical, psychological and sexual violence, decision making, negotiation, communication on household matters, gender equality and equity norms, and their relationship with women’s health. Gender based training will be addressed about transformative gender norm. Comprehensive intervention will be comprised of the advocacy meeting, community mobilization activities, husband involvement and other awareness creation activities.Advocacy meeting/workshop: will be made to convince local people who are in position (authority) (police, women association, women affair office, health professionals) that have direct contribution to tackle VAW. Research evidence that show the magnitude, associated factors and proven solutions will be presented by the principal investigator. Thorough discussions will be made on the issue of VAW as per the local setting. It will allow to convince as well as dig out implementation bottlenecks. Leaflets, posters and any other awareness creation materials will be distributed to improve community attitude about VAW.Community mobilization: will be done at different public places (church and other social gathering events) about harmfulness of VAW, gender equality and equity, women autonomy on reproductive health, decision making on household issues and negotiation/communication skill. In addition, awareness creation activities will be carried out as community conversation to reach the entire community within the study sites.Training: will be provided to community representatives as a change agent (leaders, religious fathers, elders, health care provider, police, local politicians and associations). Community believes, culture and religion are the main factors that affect attitude and gender norms. The training aims to improve awareness of public figures towards gender norm specifically on VAW. On each session of the training, discussion will be entertained to have common understanding of issues and discuss possible solutions. All trainees are expected to disseminate information while going back to their home or religious place, community gathering areas (*Idir, Equib,* etc.) and also Sunday coffee ceremonies. Regular trainings to community representatives will be given every three months for a year in each intervention group.Awareness creation information dissemination: well oriented health extension workers will implement the awareness creation activities through house-to-house by integrating with the health extension package. The awareness creation will be more focused on gender equality, equity, decision making autonomy, negotiations skill in relationship and etc. this intervention will be given mainly to the women.Husband or partner involvement on domestic violence prevention: group health education and discussions will be held with husband or partners. Gender equality, equity, decision making, communication and involving on reproductive health issues as part of human right are the main issues that will be mentioned in this target group. Women’s contribution in development and their right involving on household issues decision making will be raised and discussed.

ARM 2: Active comparator group: are all interventions listed above under comprehensive intervention (advocacy, community mobilization, awareness creation and training community representatives) will be provided to this group except active husband involvement intervention. The ultimate objective is to test the contribution of husband involvement on domestic VAW prevention.

Arm 3: Standard services (control group): the standard service will be sustained. We will regularly monitor to know what is going on in addition to the standard service during the study period for documentation purpose only.

#### Expected outcomes

**Table Taba:** 

Expected Outcomes of the Community Based Intervention	
Specific objective 1	Conduct baseline assessment of domestic VAW in the study area
	- determine the prevalence of domestic VAW (physical, sexual, psychological)
Specific objective 2	Identify associated factors of domestic VAW
	- Identify the associated factors - explore community perception - Explore stakeholders engagement level - explore implementation barriers or bottlenecks of VAW program at implementers side
Specific objective 3	Design intervention implementation strategy to tackle domestic VAW
	- Prepare the intervention material and validate according to the local culture - Integrate with community based health extension program - Conduct advocacy workshop and work with the local administrative bodies
Specific objective 4	Implement culturally acceptable interventions to address bottlenecks and DVAW
	*advocacy workshop four times a year (4 session)
	- create awareness on politicians - create champions of domestic VAW prevention - enhance commitment to implement policy documents at community level
	*community mobilization monthly for a year (12 sessions)
	- involving the community in the domestic VAW prevention - engaging stakeholders - create community ownership
	*Awareness creation to the women (at least once per month)
	- enhance their communication and negotiation skill - enhance their awareness about gender equality - transform their wife-beating acceptance attitude
	*involving husbands (6 to 12 sessions)
	- participate husbands/partner as change agent - enhance their awareness about gender equality - improve masculine attitude and transform
Specific objective 5	To assess the outcome of community based intervention on domestic VAW
	- conduct endline assessment - perform data analysis to determine the prevalence of domestic VAW - compute the difference between endline and baseline (prevalence, community acceptance, factors) - integrate with health extension program - scale up to other sites - learn from success and failure

**Table Tabb:** 

Phase 1: Baseline	Phase 2: intervention implementation	Phase 3: endline	Phase 4: dissemination and scale up
-Baseline data collection -Instrument validation -Contextualization of the intervention -explore community perceptions	-advocacy meeting with local administrative bodies and stakeholders to explore implementation barriers and also enhance engagement of stakeholders -community mobilization -awareness creation to the women on gender equality, rights and community norm -awareness creation and enhance husband/partner involvement -Training of community representatives to involve them in the traditional norm change agent -traditional coffee ceremonies and community conversation	-endline data collection - statistical analysis to investigate the intervention effect between baseline and endline -identify barriers and enablers for the future domestic violence prevention	*Dissemination
			-Advocacy meeting -policy Brief -publication in peer review journals -local Media -use social media -present in conference s
			*Scale up of successful experiences
			-learn from barriers and propose alternative solutions -integrate with health extension program -engaging stakeholders/ community
M& E	M& E	M& E	
-measurement tool and intervention material validation -number of women interviewed per day and completeness and consistency of questionnaire	-number of advocacy workshop -pre-posttest of the participant -feedback from participants -number of women involve in awareness creation -number of community representatives trained and involve on community mobilization -number of husbands/involved and attend awareness creation program - implementers briefing and debriefing regular session -KII and FGD on the progress of the intervention and acceptability of the intervention by the community	-re-orientation of data collectors -use same data collectors and same site -using same household and make sure that the women is the former participant -determine prevalence of domestic VAW -identify barriers -determine difference in difference -note that; the control group will be monitored regularly on what is going on in addition to the standard care and findings will be documented using reporting checklist.	

